### Sample size calculation

To estimate the sample size, a-priori power analysis is performed on the data from previous AOT [8, 11] and MT literature [17, 24] in stroke rehabilitation. Based on the previous data of the treatment effects on motor function outcomes (e.g., FMA), an effect size (*d*) of 0.60 to 0.95 is expected which corresponds approximately to an effect size (*f*) of 0.30 to 0.50 for a study design of three-group comparisons. An estimate of sample size requirements for each group in a three-group study design, given a power of 0.80 and a two-sided type-I error of 0.05, will be in the range of 21 to 36 patients. We therefore plan to recruit 30 participants in each group (a total of 90) in this study.

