### Randomization

The participants will be randomly allocated to one of the three treatment groups in a 1:1:1 ratio after baseline evaluation. The participants will be pre-stratified on the basis of the severity of UE motor deficits (FMA score: 20 to 40 (moderate-to-severe) versus 40 to 60 (mild-to-moderate) [28]) and side of lesion (right versus left) to assure baseline equivalence between the groups. The random assignments will be performed online using a web-based randomization tool (freely available at https://www.randomizer.org/). A research assistant who will not be involved in outcomes assessment or screening of subjects will independently manage the randomization procedure according to allocation concealment.

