### Data analysis

An intention-to-treat analysis will be performed. Two-way repeated measures analysis of variance (ANOVA) will be used to evaluate the treatment effects among the three treatment groups at the three assessments from different time points. The between-subject factor will be the group and the within-subject factor will be the time. The treatment efficacy will also be examined by determining the number of participants whose change score reaches the minimal clinically important difference (MCID) in the clinical outcomes, by using a chi-square test. The MCID values will be adopted either for the established values of outcomes or 10% of the total scores when it has not been established. A *p* value < 0.05 will be considered as indicating statistical significance.

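### The sample-size figures do not agree: f = 0.50 needs 14 per group, not 21; f = 0.50 is too large for d = 0.95; and 30 per group falls short at f = 0.30

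*Protocol article*

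**What the plan says.** All the figures are in the protocol article, under Sample size calculation. From earlier AOT and MT studies, "an effect size (*d*) of 0.60 to 0.95 is expected". This is said to correspond approximately to an f "of 0.30 to 0.50 for a study design of three-group comparisons". The number required per group, "given a power of 0.80 and a two-sided type-I error of 0.05", "will be in the range of 21 to 36 patients". The section concludes: "We therefore plan to recruit 30 participants in each group (a total of 90) in this study".

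Under Randomization, patients are "randomly allocated to one of the three treatment groups in a 1:1:1 ratio", so the groups are equal in size. Under Data analysis, the model is stated as: "Two-way repeated measures analysis of variance (ANOVA) will be used to evaluate the treatment effects among the three treatment groups". The article does not name the d-to-f formula, the pattern of group means, or the test behind the sample size.

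**The concern.** The paragraph is a chain: d gives f, f gives n per group, and n leads to 30. Each link can be checked from the printed numbers, and two do not hold.

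- **f to n.** The lower n is not the number that the upper f requires.
- **d to f.** The f range looks like d halved. That is the relation for two groups, yet it is offered for three. With three groups the same d usually gives a smaller f, so the error runs in the optimistic direction.

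The planned 30 also lies below the upper figure of the plan's own range, and the text does not say what power 30 gives there. This paragraph is the article's only justification for the sample size. It will be consulted when a null or borderline Fugl-Meyer result is interpreted, so the reader needs to know which effects 90 patients can detect.

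**Working it through.** **Inputs.** d = 0.60 to 0.95, f = 0.30 to 0.50, power 0.80, alpha 0.05, 21 to 36 per group required and 30 planned (Sample size calculation); three equal groups (Randomization).

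**Method.** One-way omnibus F test with k = 3 and n per group, N = 3n, degrees of freedom 2 and N − 3, noncentrality λ = f² × N. Power is the probability that the noncentral F exceeds the 5% critical value.

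**Step 1: reproduce the stated n from the stated f.**

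| f | n per group for 80% power | Power around the stated n |
|---|---|---|
| 0.30 | 37 (0.803) | 0.792 at 36 |
| 0.40 | 22 (0.818) | 0.798 at 21 |
| 0.50 | 14 (0.803) | 0.944 at 21 |

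The stated 36 is reproduced to within one patient. The stated 21 is not: at f = 0.50, λ with 14 per group is 0.25 × 42 = 10.5, which already suffices, while 21 per group gives λ = 0.25 × 63 = 15.75 and 94% power. The figure 21 fits f of about 0.40, which the article does not state.

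Other routes were tried, and none gives 21 and 36 together from f = 0.50 and 0.30:

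- alpha 0.10: 12 and 30
- power 0.90: 18 and 48; power 0.95: 22 and 59
- one covariate, counting only the lost degree of freedom: 14 and 37
- repeated-measures between-group test, three times, correlation 0.5: 10 and 25; correlation 0.9: 14 and 35
- group-by-time interaction, three times, correlation 0.5: 4 and 9
- 30% dropout added to 14 and 37: 20 and 53
- pairwise comparison directly on d = 0.95 and 0.60 (normal approximation): 18 and 44 two-sided, 14 and 35 one-sided, 22 and 53 with alpha halved

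**Step 2: from d to f.** With common standard deviation σ, f is the root mean squared deviation of the group means from their average, divided by σ.

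- Two groups: f = d/2, so 0.60/2 = 0.30 and 0.95/2 = 0.475. Rounded up, this is the stated range.
- Three groups with means 0, d/2, d: f = d/√6 = 0.408d.
- Three groups with means 0, d, d: f = d√2/3 = 0.471d.

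If d is the largest of the three pairwise differences, every pattern lies between the last two.

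| d | f, three groups | n per group for 80% power | Power at 30 per group |
|---|---|---|---|
| 0.60 | 0.245 to 0.283 | 55 to 42 | 0.52 to 0.65 |
| 0.95 | 0.388 to 0.448 | 23 to 18 | 0.91 to 0.97 |

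**Step 3: what 30 per group gives.** At the plan's own f = 0.30, λ = 0.09 × 90 = 8.1 and power is 0.707. Power reaches 0.80 at f = 0.333. In terms of d this is 0.333/0.471 = 0.71 to 0.333/0.408 = 0.82, depending on the pattern of means.

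**The case against.** **The upper n is sound.** A reader might infer that the n range is wrong at both ends. It is not: 36 against 37 is rounding. The 21 also lies inside the 18 to 23 that d = 0.95 needs after a three-group conversion. It contradicts the printed f = 0.50 but is not clearly too small for the printed d.

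**The d/2 formula is an inference.** The article names no formula, says the correspondence is approximate, and prints 0.50 where d/2 gives 0.475. The match is suggestive, not proof. A reader might also suppose that d came from two-arm studies; the article cites AOT and MT literature without giving the number of arms, so that cannot be claimed.

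**d need not be the largest difference.** If 0.60 is the smaller of two unequal effects against control, f = 0.30 can be reached. As an illustration with assumed means, 0, 0.60 and 0.667 give f = 0.300 and 37 per group; 0, 0.60 and 0.95 give f = 0.392 and 22 per group. This stands, and it makes the 42 to 55 conditional. It does not rescue the upper value: with 0.95 as the largest effect, f cannot exceed 0.448.

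**The planned analysis is not a one-way ANOVA.** Data analysis specifies three groups by three times. Baseline information could raise power: on an assumed baseline correlation of 0.5 to 0.7, a baseline-adjusted one-way comparison at d = 0.60 with 30 per group would have power of 0.65 to 0.83 (f = 0.245) or 0.78 to 0.92 (f = 0.283). The article gives no correlation, so a reader should not conclude that the trial is underpowered outright. Nor does the article claim 80% power at d = 0.60 with 30 per group; 30 is a choice within the stated range. None of this makes 21 the requirement for f = 0.50.

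**Conclusion.** The paragraph is wrong as written, in a limited way.

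- **Firm, on the printed figures under a one-way omnibus test:** f = 0.50 requires 14 per group, not 21, while 36 agrees with f = 0.30. None of the alternative calculations tried reconciles the two ranges. On the same basis the planned 30 is below the plan's own upper requirement, with about 71% power at f = 0.30 and 80% only at f of about 0.33.
- **Conditional on d being the largest standardised difference among three equal groups:** f = 0.50 is out of reach for d = 0.95 (maximum 0.448), and d = 0.60 gives f = 0.245 to 0.283, needing 42 to 55 per group without baseline adjustment.
- **Inferred only:** that the authors halved d.

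The documents do not support saying that the n range fails at both ends or that 90 patients are too few for the planned analysis. They support saying that the stated derivation does not lead to 30 per group with 80% power across the effects named.

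**What to change.** Rewrite the Sample size calculation paragraph:

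1. State which difference d refers to, the assumed pattern of the three means, and the test that the calculation is for.
2. Replace the f and n ranges with a matching pair. For example, with both active arms equal and better than control, f = 0.28 to 0.45, needing 42 down to 18 per group. This pattern is only an illustration; the sponsor should state its own.
3. State the power of 30 per group at each end. Under that example, for a one-way comparison without baseline adjustment, it is about 65% at d = 0.60 and 97% at d = 0.95, with 80% at d of about 0.71.
4. If credit is taken for baseline or repeated measurements, state the assumed within-patient correlation and show power over a plausible range.

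The cost is one paragraph of text. Recruitment, allocation and the planned analysis stay as they are; the stated power at the cautious end becomes less favourable.

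### The 0.80 power target is not tied to either effect of the planned repeated-measures ANOVA, and 30 per group gives about 71% at the plan's lower effect size even for a plain three-group comparison

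*Protocol article*

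**What the plan says.** **Sample size calculation.** The article states that "an effect size (*d*) of 0.60 to 0.95 is expected" and converts this to an f of about 0.30 to 0.50 "for a study design of three-group comparisons". The requirement per group, "given a power of 0.80 and a two-sided type-I error of 0.05", "will be in the range of 21 to 36 patients". It concludes: "We therefore plan to recruit 30 participants in each group (a total of 90) in this study". The section mentions no repeated assessments, no within-patient correlation and no named effect of the analysis.

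**Data analysis.** "Two-way repeated measures analysis of variance (ANOVA) will be used to evaluate the treatment effects among the three treatment groups", with group as the between-subject factor and time as the within-subject factor. The three time levels are baseline, the end of the 3-week treatment, and 3 months later. Under Randomization, allocation follows the baseline evaluation. The section sets significance at p < 0.05 and does not say which ANOVA effect carries the treatment conclusion.

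**The concern.** A 3 × 3 repeated-measures ANOVA offers two tests that could be read as the treatment effect: the group main effect (2 numerator df), averaged over all three visits, and the group-by-time interaction (4 numerator df). Randomised groups have equal expected scores at baseline. Including that visit therefore dilutes the group main effect, and a higher correlation between visits lowers its power. The interaction behaves in the opposite way, gaining power as correlation rises. No single power figure can stand for both.

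The sizing inputs describe neither test. The reader cannot tell what the 0.80 refers to or how much power 30 per group has for the test that will decide efficacy. Two eligible tests at the same 0.05 threshold also leave room to choose between them once the results are known.

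**Working it through.** **Inputs from the article:** two-sided alpha 0.05; target power 0.80; f = 0.30 to 0.50; stated 21 to 36 per group; chosen n = 30 per group (N = 90); three groups at 1:1:1; three visits, including baseline.

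**Assumptions, because the article gives none:** within-patient correlation ρ from 0.3 to 0.9; compound symmetry; equal baseline means; f on the raw-score SD and equal at both later visits (a sustained effect).

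**1. Reproducing the stated range.** One-way F test, noncentrality λ = 3n·f², df 2 and 3n − 3.

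| f | n per group | λ | Power |
|---|---|---|---|
| 0.30 | 36 | 108 × 0.09 = 9.72 | 79.2% |
| 0.30 | 37 | 111 × 0.09 = 9.99 | 80.4% |
| 0.50 | 14 | 42 × 0.25 = 10.50 | 80.3% |
| 0.50 | 21 | 63 × 0.25 = 15.75 | 94.4% |
| 0.40 | 21 | 63 × 0.16 = 10.08 | 79.8% |
| 0.30 | 30 | 90 × 0.09 = 8.10 | 70.7% |
| 0.50 | 30 | 90 × 0.25 = 22.50 | 99.1% |

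The upper end (36) fits f = 0.30. The lower end (21) does not fit f = 0.50, nor f = 0.475 (half of d = 0.95), which needs 16; it fits f = 0.40. At 30 per group, 80% power needs f of about 0.333. None of this step depends on ρ.

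**2. The planned ANOVA with 30 per group.**

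- Group main effect: the visit-averaged effect is (2/3)f and the variance of a patient's mean is (1 + 2ρ)/3 of the single-visit variance. So λ = 90·f²·(2/3)² ÷ [(1 + 2ρ)/3], df 2, 87.
- Interaction: effects (0, f, f) leave a sum of squares over time of (2/3)f², and the within-patient error variance is (1 − ρ). So λ = 90·f²·(2/3) ÷ (1 − ρ), df 4, 174.
- Baseline-adjusted comparison immediately after treatment: λ = 90·f² ÷ (1 − ρ²), df 2, 86.

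Example at f = 0.30, ρ = 0.5: main effect λ = 8.1 × 0.4444 ÷ 0.6667 = 5.40; interaction λ = 8.1 × 0.6667 ÷ 0.5 = 10.80; baseline-adjusted λ = 8.1 ÷ 0.75 = 10.80.

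Power at f = 0.30:

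| ρ | Group main effect | Interaction | Baseline-adjusted, post |
|---|---|---|---|
| 0.3 | 62% | 57% | 75% |
| 0.5 | 52% | 74% | 83% |
| 0.7 | 45% | 94% | 95% |
| 0.8 | 42% | 99% | 99% |
| 0.9 | 39% | >99% | >99% |

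**3. Upper end and sensitivity.** At f = 0.50 with a sustained effect, the group main effect has 98% falling to 83% and the interaction 97% rising to above 99%. If the effect is present only immediately after treatment, (2/3)² becomes (1/3)². Main-effect power is then 19% falling to 13% at f = 0.30, and 46% falling to 28% at f = 0.50. Interaction power is unchanged, because effects (0, f, 0) leave the same (2/3)f².

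**The case against.** A reader might infer that the 0.80 is for a one-way test and belongs to no planned test, so that the trial is wrongly presented as having 80% power. The article does not support that much.

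- It never says one-way, and only the upper figure fits such a test. A repeated-measures formula for a between-group effect of f = 0.30 at every visit would give 21 at ρ = 0.3 and 36 at ρ = 0.95, so the source of the range cannot be proved.
- The 0.80 is the target that yields 21 to 36; it is not claimed for 30.
- The group factor in the ANOVA is itself a three-group comparison. For the interaction, a one-way sizing is conservative once ρ reaches about 0.5 (at f = 0.30, 74% against 71%).
- Widely different power is conditional. At ρ = 0.3 the two effects are close (62% and 57%), and at f = 0.50 with a sustained effect both exceed 80% at every ρ examined.
- The objectives concern immediate and retained effects, which suggests group-by-time change. Nothing says the baseline-averaged group effect will decide efficacy.
- If f was derived from change scores, the figures that depend on ρ would not apply.

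All of this stands and limits the claim. It does not remove the mismatch, because the article itself states both the power basis and the analysis, and they do not connect. Nor does it touch the 71% at f = 0.30 on the one-way basis, which needs no ρ. A separate analysis plan might name the confirmatory effect, but the article's power statement would still need restating for it.

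**Conclusion.** The point holds in a limited form. The 0.80 target is not tied to either effect of the planned ANOVA, and the article names no efficacy effect. On a one-way basis the stated range corresponds to f = 0.40 down to 0.30, not 0.50 down to 0.30, and 30 per group has about 71% power at f = 0.30. For the planned ANOVA at that f, power lies between 39% and 62% for the group effect and between 57% and above 99% for the interaction. Those ranges rest on equal baseline means, a sustained effect, compound symmetry, f on the raw-score scale and an assumed ρ of 0.3 to 0.9. At the upper f the choice of effect costs little if the effect is sustained. The documents do not show that the trial is underpowered across its stated range, or which test produced the 21 to 36.

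**What to change.** 1. In Data analysis, name one confirmatory test for the FMA: the baseline-adjusted three-group comparison immediately after treatment or, failing that, the group-by-time interaction.
2. State that the group main effect averaged over baseline will not be used to judge efficacy.
3. In Sample size calculation, restate the power of 30 per group for the named test over f = 0.30 to 0.50, giving the assumed correlation and its range. For the baseline-adjusted test at f = 0.30 this is 75% at ρ = 0.3, 83% at 0.5 and 95% at 0.7. Correct or explain the lower figure of 21 per group.

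**Cost:** wording and one recalculation, using assessments already planned and no more patients. The stated power will fall below 0.80 where f and the correlation are both at their low end, and the article should say so.

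### The planned 30 patients per group is below the plan's own requirement of 36 at the smallest effect it expects, so the stated 0.80 power does not hold there

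*Protocol article*

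**What the plan says.** All the relevant figures stand together under Sample size calculation in the protocol article. The expected standardised difference d is "of 0.60 to 0.95 is expected which corresponds approximately to an effect size" f "of 0.30 to 0.50 for a study design of three-group comparisons". The requirement per group, "given a power of 0.80 and a two-sided type-I error of 0.05, will be in the range of 21 to 36 patients". The conclusion follows directly: "We therefore plan to recruit 30 participants in each group (a total of 90) in this study".

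The section names no single design effect, gives no reason for choosing 30 within the range, and quotes no power other than 0.80. Under Randomization, allocation is 1:1:1. Under Data analysis, the planned method is: "Two-way repeated measures analysis of variance (ANOVA) will be used to evaluate the treatment effects among the three treatment groups", with three assessment times.

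**The concern.** A requirement that runs from 21 to 36 as the effect varies means that the largest number belongs to the smallest effect. Recruiting 30 therefore meets the requirement for the larger effects in the range and misses it for the smallest ones. The section moves from the 0.80 requirement to 30 as if one followed from the other, and does not say what power 30 gives at the low end.

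What is at stake is how a null three-group result would be read. The article's Discussion itself treats the effectiveness of both therapies as unsettled, so a null result is a real possibility. A reader who takes 0.80 at face value would assume a miss rate of at most 20% for any effect in the expected range. At the bottom of that range the rate on the plan's apparent method is nearer 29%.

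**Working it through.** **Inputs.** All come from the protocol article: three groups allocated 1:1:1; alpha 0.05; target power 0.80; f from 0.30 to 0.50; stated requirement 21 to 36 per group; planned n = 30 per group. The f values are taken as given. The article does not name the test behind its range, so the one-way three-group F test is my assumption, judged by whether it reproduces the plan's figures.

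**Formula.** With n per group, the test has 2 and 3n − 3 degrees of freedom and noncentrality λ = 3n × f². Power is the probability that a noncentral F with those parameters exceeds the 5% critical value of the central F.

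**Step 1: reproduce the upper bound (f = 0.30).**
- n = 36: λ = 108 × 0.09 = 9.72, power 0.792.
- n = 37: λ = 111 × 0.09 = 9.99, power 0.803.

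The exact answer is 37, so the plan's 36 is reproduced within one patient.

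**Step 2: try the lower bound (f = 0.50).**
- n = 14: λ = 42 × 0.25 = 10.5, power 0.803.
- n = 21: λ = 63 × 0.25 = 15.75, power 0.944.

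The same method gives 14, not 21. A requirement of 21 corresponds to f of about 0.40 (λ = 63 × 0.16 = 10.08, power 0.798). Two-sample t tests (one- and two-sided, with and without adjusted alpha) and repeated measures variants with assumed correlations were also tried. None reproduced both ends of the range from the stated inputs.

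**Step 3: power with the planned n = 30 (λ = 90 × f²).**

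| f | λ | Power |
|---|---|---|
| 0.30 | 8.10 | 0.707 |
| 0.333 | 9.98 | 0.800 |
| 0.35 | 11.03 | 0.840 |
| 0.40 | 14.40 | 0.926 |
| 0.50 | 22.50 | 0.991 |

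The smallest f with 80% power is 0.333. The part of the stated range that reaches 80% is (0.50 − 0.333) / (0.50 − 0.30) = 0.167 / 0.20, about five-sixths. The miss rate at f = 0.30 is 1 − 0.707 = 0.293.

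**Step 4: distance from the plan's own requirement.** At f = 0.30 the plan's figure implies 3 × 36 = 108 patients, or 3 × 37 = 111 by the exact calculation, against 90 planned.

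**Sensitivity to loss (assumption; the article gives no rate).** If 10% or 20% were lost, leaving 27 or 24 per group, power at f = 0.30 would be 0.66 or 0.60, and the smallest f with 80% power would be 0.35 or 0.37.

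**The case against.** The strongest reply is that the section never says 30 gives 80% power over the whole range. It discloses the 36, picks a number above the midpoint of its range ((21 + 36) / 2 = 28.5), and leaves the reader to see that 30 is less than 36. A compromise under an uncertain effect is a legitimate planning choice. This stands in part: a reader might infer a promise of 0.80 power throughout the range, and the text does not make that promise in words. What remains is that 0.80 is the only power given, 30 is presented as its consequence, and the power at the low end is left unstated.

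Second, the planned analysis is a repeated measures ANOVA, not a one-way test. For its between-group term with three assessments, λ = 90 × f² × 3 / (1 + 2ρ). At f = 0.30 this gives power of 0.88, 0.81 and 0.74 for assumed within-patient correlations ρ of 0.5, 0.7 and 0.9. If 0.30 were instead the effect size of the group-by-time interaction, power would be higher still (at least 0.985 in the variants tried), but the article does not define f that way. This objection also stands in part. The 71% must not be read as the power of the planned analysis. It does not remove the inconsistency, because the article states no correlation and its 36 matches the one-way calculation. Whichever method produced 36, the plan asks for 36 at the low end and recruits 30.

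Third, a reader might conclude that the trial is underpowered because dropout is ignored or because pairwise comparisons would have less power. The document does not support either as a finding. It speaks of recruiting 30, not of analysing 30. An attrition allowance may well sit in the full protocol. The section sizes a three-group comparison, and no multiplicity rule for pairwise contrasts appears in the article.

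**Conclusion.** The point holds in a limited form. On the section's own figures, 30 per group does not meet the 0.80 requirement at the smallest expected effect. On the one-way test that matches the 36, power there is about 71%, and 80% is reached from f of about 0.33. The shortfall covers roughly the lowest sixth of the stated range; from f = 0.35 upwards power is 0.84 or more.

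The documents do not support the stronger reading that the trial as a whole lacks 80% power. The sizes given rest on complete data, on the article's f values taken as given, and on a one-way approximation to the planned analysis. The lower bound of 21 is a separate error by that method, but it makes the requirement too large, not too small, and does not affect the conclusion at the upper end. Severity is moderate: no estimate or decision rule depends on it, but the stated power is part of how an inconclusive result will be read.

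**What to change.** Keep 90 patients and replace the link between the 0.80 requirement and 30 with the power that 30 delivers. Suggested text: *30 per group gives 80% power for f of about 0.33 and above and about 71% at f = 0.30 (one-way three-group F test, complete data; the power of the repeated measures analysis depends on a within-patient correlation that is not stated).* If the sponsor has a correlation in mind, state it and give the power of the planned analysis in the same sentence.

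Recompute the lower bound at the same time: f = 0.50 needs about 14 per group by this method. If 21 came from another method or effect size, name it. Any statement on attrition should appear only as a sensitivity result with its assumed loss rate given.

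The cost is a change of wording and a less favourable published figure at the low end of the range. No extra patients and no change to design or analysis are needed.
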